### Costing analysis

A costing analysis is also included in the study protocol. Trained research assistants have been identifying human, financial, physical, and time resources required for the HCP delivered program throughout the study. Data has been collected and categorized by research-related costs or operational costs in order to calculate the monetary value of resources needed to conduct the intervention. The costs and effectiveness of this approach will be compared between treatment versus control groups and will mirror methodology from a previous cost-effectiveness analysis of an IPV intervention
[46]. This costing exercise will provide insight into the scalability of the intervention and economic impacts of broader policy recommendations.

## Discussion

This study seeks to train and improve nurses’ capacities to deliver an intervention for women currently experiencing IPV that present at health clinics in Mexico City. If found efficacious, this study may have an important influence on programming and policy for the health sector responses in city-based clinics serving low-income women in the region. Findings may also contribute to the evidence-base for comprehensive prevention strategies to reduce IPV and to respond to the needs of survivors. This intervention may be an effective health-sector tool to reduce IPV and mitigate negative effects, in addition to many other approaches including changes in the legal system or other social change approaches that focus on gender equality and the engagement of men to reduce violence
[47–49].

Despite the strong study design to assess the efficacy of the HCP delivered intervention on outcomes, limitations and potential problems have been considered. As with other randomized controlled trials, participant drop-out and differential attrition is a concern
[19]. To address potential problems, we have added an exclusionary criterion that women do not plan on relocating within the study period. At the time of enrollment, we also verify contact information for the woman and obtain information for three additional contacts that would know how to get in touch with her. In the analysis plan, we will assess for differential attrition and potentially adjust final models for variables that may have statistically differed between treatment arms. Other approaches may also be used to handle missing data, including multiple imputation, which has been used in other studies examining IPV screening effectiveness
[15].

In addition, staff at referral community agencies that are aware of and engaged with the study may also turnover, which may have a bearing on the quality of service provision. As noted in literature regarding health sector responses to IPV, linkages to community agencies may be a critical component of success
[29]. While there are agencies for referral in Mexico City, including UAVIF, the quality of services received at referral community agencies remains unclear as it is outside the scope of the current study. In addition, there may be challenges in the capacity of referral agencies to respond to significant increases in referrals. Nonetheless, we will be able to assess utilization of agency services through the quantitative assessments with participants and gain insight into experiences through qualitative interviews. Within the clinics themselves, pilot work revealed the lack of private spaces as a physical challenge of conducting the survey and administering the HCP delivered intervention. While the study team has worked with clinic staff to identify private spaces to maintain confidentiality of participants, considerations of space must be addressed if the intervention were to be scaled up. Similar challenges have been noted elsewhere
[28, 29] among health clinic interventions in low and middle income countries.

Another potential limitations that may affect our ability to see changes in IPV, that result from the intervention, is the limited follow-up time of the intervention. IPV, as noted by others
[50], is a complex issue that may often require many attempts to leave an abusive partner. Thus, changes in IPV may be difficult to discern given the twelve-month follow-up after the second counseling session. However, our selection of secondary outcomes including changes in use of community resources and safety planning behaviors will allow us to see potential changes that may occur on the pathway to eventually leaving a partner. Nonetheless, statistically significant changes in other secondary outcomes, such as quality of life, may also be difficult to discern in the short follow-up period. For instance, housing relocations, childcare considerations, *etc.* may also have a negative influence on quantitative measures of quality of life as a result of leaving an abusive partner. However, qualitative interviews among women at the follow-up period will provide a meaningful narrative of women’s intervention-related experiences and attempts to leave their abusive partner. The mixed methods approach to understanding intervention impacts may be important, particularly for quality of life, as previous studies have documented null associations between quality of life and IPV screening
[51].

In addition, due to logistical constraints, we could not train all personnel at health clinics, thus this is not a system-wide intervention. Therefore, we are limited concerning inferences we can make regarding institutional changes necessary for comprehensive health sector responses to IPV. MoH clinics were not able to send all nurses to the training even when trainings on different dates were held, nor were we able to train all front-line staff at the clinics. Consequently, we focused our efforts on recruiting non-field based nurses who have the highest probability of seeing the most patients in the clinic and were on morning shifts. Nonetheless, we will be able to test the potential efficacy of an HCP delivered program on IPV and related outcomes in an urban, middle-income country health system setting. If proven to be a feasible approach, future studies and monitoring efforts could be built into scale-up of activities among all nurses at health clinics. This first step is particularly feasible given the MoH’s investment in IPV programs. In addition, our ongoing process evaluations and training to nurses will provide a supportive environment to increase their efficacy to address IPV.

In summary, this trial will seek to train and increase capacity of nurses in Mexico City to identify and respond to IPV and generate evidence if such an approach is effective in reducing IPV and mitigation of related health concerns. If found to be efficacious, the study may offer important contributions and insights regarding how to increase the capacity of the health sector to respond to survivors of IPV in Mexico City. Ultimately, the results of this trial will contribute to global knowledge on the key role of HCPs in addressing IPV.

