## Background

Intimate partner violence (IPV) against women is a critical health, human rights, and development concern, with global estimates indicating that approximately one in three women have reported such violence at some point in their life
[1]. Research has documented a range of negative health effects from IPV, including poor mental health, unwanted pregnancies, reproductive coercion, and vulnerabilities to HIV and sexually transmitted infections
[2–7]. Within Mexico, approximately 25%-40% of women who receive health sector services have reported violence from their partners at some point in their life
[8–10]. These lifetime IPV figures are comparable to other countries in Latin America and the Caribbean
[11], and underscore the importance of interventions in health care settings. These approaches are critical as women experiencing IPV have been shown to disproportionately utilize health care services
[12], and providers may be in a unique opportunity to intervene as they are among the few outside contacts a woman may have exposure to.

Despite the potential importance of health care provider (HCP)-delivered IPV interventions and in particular, HCP IPV screening programs, such approaches remain controversial
[13, 14]. Much of the debate surrounding the screening of women for IPV by HCPs is due to mixed evidence regarding the effectiveness of such approaches in reducing IPV and improving health outcomes
[15, 16]. Moreover, IPV screening by HCPs is not universally recommended by professional health organizations
[17]. However, it remains unclear if the screening alone is an ineffective approach for addressing IPV or if HCPs do not fully adhere to screening protocols. Lack of fidelity towards consistent screening has been noted in systematic reviews due to a variety of barriers perceived by HCPs
[18]. In addition, as studies evaluating screening for IPV involve vulnerable populations of abused women, there may be high levels of attrition
[15], which may vary differentially by severity of IPV victimization and thus limit extrapolation of findings. However, the evidence-base is growing to suggest that comprehensive and systems-approaches to identifying and counseling women experiencing IPV in health settings is an effective strategy
[19–21] to address both IPV victimization and related health concerns.

Thus, rigorous evaluations, including randomized controlled trials, of these combined and integrated HCP approaches are needed

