### Randomization, sample size, and power analysis

Approximately 900 women from 42 health clinics were calculated to be sufficient sample size in order to achieve 80% power to detect a 15% difference in IPV frequency between treatment versus control arms at the α < 0.05 statistical significance level. A conservative intraclass correlation of 0.07 was assumed for clustering at the clinic level. This total sample size takes into account an attrition rate of 45%. The study proposal has budgeted for tracking participants that are relatively more difficult to track in order to reduce attrition.

Health clinics were first stratified by city zone (e.g. Center, North, East, West, South). Of the 57 health clinics that met inclusion criteria, 42 were randomly selected and randomized to treatment or control conditions, based on sample size calculations. To select the 42 health centers, all centers were assigned random numbers in Excel and sorted from smallest to largest; health centers were selected based on city zone and in order of their random number. Randomization was completed in STATA.

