### Quantitative assessments & analytic plan

Our primary outcome is past-year IPV
[32] and our secondary outcomes include past-year reproductive coercion
[7, 23], use of community-based resources
[33], safety planning measures
[33], and quality of life
[34]. Descriptive statistics will be used to assess achievement of Aim 1. For the remaining aims, the follow analyses plans will be undertaken: (1) assess if randomization of health clinics was successful by examining if there are statistically significant differences between women’s demographics, by treatment arm, through chi-square or t-tests; (2) assess for differential loss to follow up by demographics and baseline IPV severity; (3) assess if IPV and secondary outcomes (reproductive coercion, safety planning, use of community resources, quality of life) differed at baseline, by treatment arm; and (4) conduct multilevel analyses of the effect of the intervention on outcomes utilizing appropriate models that will account for potential clustering for repeat measures, time, and at the clinic level. We will subsequently estimate adjusted models if any demographics significantly varied at baseline. Analyses will first be undertaken using the intent-to-treat approach. Following this, a per protocol analysis will be undertaken to determine whether effectiveness varied by adherence (i.e. attending the three month booster counseling session) and potentially nurse adherence.

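### Significant between-arm differences are the wrong trigger for covariate adjustment when dropout may depend on baseline IPV severity

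*Protocol article*

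**What the plan says.** **Size and expected loss.** Under Randomization, sample size, and power analysis, the protocol article states: "Approximately 900 women from 42 health clinics were calculated to be sufficient sample size in order to achieve 80% power". The target is to "detect a 15% difference in IPV frequency between treatment versus control arms at the α < 0.05 statistical significance level", and "A conservative intraclass correlation of 0.07 was assumed for clustering at the clinic level". On loss to follow-up: "This total sample size takes into account an attrition rate of 45" per cent.

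**Severity and loss.** The Background says of attrition in studies evaluating IPV screening that it may be high, "which may vary differentially by severity of IPV victimization and thus limit extrapolation of findings". Under Quantitative assessments & analytic plan, the second step is to "assess for differential loss to follow up by demographics and baseline IPV severity". No later step says what follows if such loss is found.

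**Model and adjustment.** The same section will "conduct multilevel analyses of the effect of the intervention on outcomes utilizing appropriate models" that account for repeated measures, time and clinic. Adjusted models follow if a demographic variable differs significantly between arms at baseline. The Discussion returns to attrition: "we will assess for differential attrition and potentially adjust final models for variables that may have statistically differed between treatment arms". Its next sentence adds that other approaches to missing data, multiple imputation among them, may also be used.

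**Entry criterion.** Under Study population, recruitment, and retention, every woman must report physical or sexual IPV in the past year.

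**The concern.** A covariate is needed to handle dropout when it predicts both who is lost and what the outcome would have been. Whether it differs significantly between arms at baseline is a separate question. Baseline IPV severity is the obvious candidate, and the plan itself singles it out for the loss check. Yet randomisation tends to balance it, and the trigger in the analytic plan covers demographics only, so severity would usually stay out of the model.

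The multilevel model does not by itself fill the gap. All women are IPV-positive at entry, so a binary baseline outcome is constant and says nothing about severity. Severity has to enter as a covariate, as an imputation variable or through a graded outcome, and the article commits to none of these.

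At stake is the primary comparison. If more severely abused women drop out at different rates in the two arms, the retained groups differ in severity and a difference in 15-month IPV appears without any treatment effect.

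**Working it through.** **1. The plan's own figure.** Inputs from the sample size section: 900 women, 42 clinics, intraclass correlation 0.07, 45% attrition.
- Analysed: 900 × 0.55 = 495. Per clinic: 495/42 = 11.79.
- Design effect: 1 + (11.79 − 1) × 0.07 = 1.755.
- Effective number per arm: 495/1.755/2 = 141.

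The control rate is not stated, nor whether 15% is absolute or relative. Assuming 80% against 65% and a two-sided test, the pooled rate is 0.725 and the power is Φ[(0.15 − 1.96 × √(2 × 0.725 × 0.275/141)) / √((0.80 × 0.20 + 0.65 × 0.35)/141)] = 80.9%. About 900 is therefore plausible, though not uniquely reproducible. For an absolute 15-point difference, power is 71.4% to 77.0% for control rates of 40% to 75%, and 91.7% at 90%. The figure serves here only to fix the setting.

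**2. Assumed illustration.** The documents give no severity distribution or outcome rates, so these are assumptions: 50% of women severe in both arms; 15-month IPV 75% if severe and 45% if less severe; no treatment effect; 45% lost in each arm.

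Severe share among women retained = 0.5 × r_sev / (0.5 × r_sev + 0.5 × r_less). Expected IPV = 0.45 + 0.30 × that share.

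| Retention, severe/less severe | Severe share retained, control; treatment | IPV, control; treatment | Spurious difference |
|---|---|---|---|
| Control 55/55, treatment 47.5/62.5 | 50.0%; 43.2% | 60.0%; 58.0% | −2.0 points |
| Control 55/55, treatment 40/70 | 50.0%; 36.4% | 60.0%; 55.9% | −4.1 points |
| Control 70/40, treatment 40/70 | 63.6%; 36.4% | 64.1%; 55.9% | −8.2 points |
| Both arms 40/70 | 36.4%; 36.4% | 55.9%; 55.9% | 0 |

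Within each severity stratum the true difference is zero, so standardising to a common severity mix removes the bias in every row.

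**3. How often a baseline test selects severity.** With about 450 women per arm, significance needs a gap of 1.96 × √(0.25 × 2/450) = 6.5 points in the severe share. Under randomisation that happened in about 5% of simulated trials.

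**4. Simulation of the rule.** 1,500 trials per scenario, 42 clinics, 900 women, intraclass correlation about 0.07, no effect, cluster-robust standard errors. Here severity itself was allowed to trigger adjustment, which is more generous than the demographics-only wording.

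| Scenario | Trigger rule: bias; type I error | Severity always adjusted: bias; type I error |
|---|---|---|
| Control 55/55, treatment 40/70 | −4.1 points; 11.5% | −0.2 points; 4.8% |
| Control 70/40, treatment 40/70 | −7.6 points; 27.4% | +0.1 points; 5.3% |
| Both arms 40/70 | −0.1 points; 5.1% | −0.1 points; 5.7% |

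The Monte Carlo standard error at 5% is √(0.05 × 0.95/1500) = 0.6 points. If severity can never trigger adjustment, the first two rows become −4.3 points with 11.8%, and −8.0 points with 28.5%.

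The simulation analyses the 15-month outcome alone and does not fit the planned repeated-measures model. Three-month data could reduce the bias to an extent not estimated here.

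**The case against.** **The remedy is a set of options.** A reader might infer that between-arm adjustment is the only response to attrition. It is not: multiple imputation is named in the next sentence, and loss by severity will be examined. What stands is that both adjustment and imputation are optional, and that the one criterion actually stated is the wrong one.

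**The Discussion phrase is ambiguous.** It does not say that the difference must be at baseline. If it means differences among women retained, severity could be selected. With 247.5 retained per arm, a gap of 50.0% against 36.4% gives z = 0.136/0.0441 = 3.09, so the test triggers about 87% of the time. Under opposite patterns it nearly always triggers. In the mildest row, 50.0% against 43.2%, z = 1.52 and it triggers about 33% of the time. This reading would remove much of the larger biases, but the analytic plan's own trigger concerns baseline demographics, and the adjustment remains only potential.

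**Bias needs dropout patterns that differ by arm.** This is correct under no effect. Counselling in one arm and unblinded research assistants make such a difference possible, but nothing shows that it occurred. A reader might infer that treatment women are called back more often. The article does not support that: both arms are surveyed at three months, and all women receive the same monthly reminder calls.

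**The analysis is not simply of completers.** A reader might infer that the intent-to-treat result is really a completer result. A repeated-measures model can use women seen at three months and lost later, so that goes too far.

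**Generic worst-case arithmetic does not measure this fault.** One could note that a 15-point completer effect shrinks to 0.55 × 15 = 8.25 points if missing women had no benefit, or vanishes if missing treatment women did 15 × 0.55/0.45 = 18.3 points worse than missing controls. That holds for any trial with 45% missing, whichever covariates are used.

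**Other limits.** The 45% is a planning allowance, and the article describes tracking measures to reduce loss. The Background remark on severity concerns published studies; it does not predict this trial's loss. Loss tables and an analysis for dropout that depends on unobserved violence may be in an analysis plan not shown.

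**Conclusion.** The concern holds in limited form. A significant difference between arms is the wrong criterion for choosing covariates to handle attrition, and the plan attaches no action to its own check of loss by baseline severity. Read as a baseline trigger, the rule would leave severity out about 95% of the time, or always if only demographics count.

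The consequence is conditional. Under the assumptions shown, with patterns of 40/70 in treatment against 55/55 or 70/40 in control, the spurious effect is about 4 to 8 points. That is substantial against a 15% target if it is read as absolute points. A milder pattern gives about 2 points, and identical patterns in both arms give essentially none under no effect. These sizes depend on assumed severity shares, outcome rates and retention. They are not estimates of bias in this trial. The change is worth making because it uses data already collected and does not depend on which pattern occurs.

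**What to change.** Remove significance testing as the trigger for adjustment in both the analytic plan and the Discussion. State in advance that the primary analysis will do one of the following:

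- include baseline IPV severity, city zone (the stratification factor) and a named list of other recorded predictors of dropout as covariates in the multilevel model; or
- use a multiple imputation model that respects clinic clustering, is fitted by arm, and contains those variables and the three-month measures.

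Whichever is chosen should be a commitment, and the check of loss by severity then becomes descriptive. According to Trial status, baseline and three-month surveys were complete at resubmission, so the predictor list can be fixed from three-month loss without reference to 15-month outcomes.

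The cost is modest extra programming. If the model is logistic, covariate adjustment changes what the odds ratio measures, so a standardised risk difference should be reported alongside it. A delta-adjusted sensitivity analysis, with the shift varied separately by arm, would be a useful addition but is secondary to this point.

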### Trial status

Study recruitment is currently underway at the time of initial manuscript submission. Upon resubmission, the baseline and three-month follow-up surveys have been completed.

## Abbreviations

HCP: Health care provider
IPPF/WHR: International Planned Parenthood Federation/Western Hemisphere Region
IPV: Intimate partner violence
MoH: Ministry of Health.
